### Study analysis

The intervention will be evaluated following the recent guidance on process evaluation for complex interventions [86]. Data will be analysed using generalized linear mixed modelling (GLMM) [87] with a 4 (condition: control, motivation, self-regulation, habit) × 2 (time: baseline, 3-month follow-up) mixed-model design, accounting for nesting within hospital. Models will be conducting to compare change between conditions of the primary outcome (physical activity) and secondary outcomes (e.g., theory-derived psychological constructs, DASS21, MOS-SF12, and absenteeism). Mediation analyses will be conducted using path analytic models using Preacher and Hayes’ bootstrapped approach for multiple mediation [88]. Separate path models will be conducted for each condition. Each condition will be represented by a dichotomous dummy-coded variable (0 = did not receive intervention component, 1 = received intervention component). Each condition variable will be set as a predictor of physical activity at follow up with motivation and intention (motivation condition), perceived behavioural control and planning (self-regulation condition), and self-reported habit (habit condition) as multiple mediators in each analysis, respectively. Baseline physical activity will be included as a control variable. Intention-to-treat (baseline carried forward) will be utilised for missing data from drop-out. Other missing data will be imputed using multiple imputation with chained equations [89]. Both intention-to-treat and completers analyses will be reported.

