**Methods/Design:**

Healthcare professionals (*N* = 192) will be recruited from four hospitals in Perth, Western Australia, via email lists, leaflets, and posters to participate in the four group randomised controlled trial. Participants will be randomised to one of four conditions: (1) education only (non-tailored information only), (2) education plus intervention components to enhance motivation, (3) education plus components to enhance motivation and self-regulation, and (4) education plus components to enhance motivation, self-regulation and habit formation. All intervention groups will receive a computer-tailored intervention administered via a web-based platform and will receive supporting text-messages containing tailored information, prompts and feedback relevant to each condition. All outcomes will be assessed at baseline, and at 3-month follow-up. The primary outcome assessed in this study is physical activity measured using activity monitors. Secondary outcomes include: quality of life, stress, anxiety, sleep, and absenteeism. Website engagement, retention, preferences and intervention fidelity will also be evaluated as well as potential mediators and moderators of intervention effect.

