### Study design

The *PATHS* study is a pragmatic four-group intervention trial adopting a randomised control design with assessments of primary and secondary outcomes at baseline and 3-month follow-up time points (see Fig. 1). We chose randomisation of individuals within hospitals (rather than randomisation of hospitals or wards) because individual randomisation was more efficient and more feasible with continuous recruitment of the participants; program was delivered to individuals rather than groups so contamination across intervention groups was not considered a major risk [46]. The project comprises three intervention conditions and a no intervention condition, in which participants receive information about the study only. This will serve as a control condition. Each condition includes a group of theory-based BCTs designed to test the additive effects of the specific BCT groups on study outcomes:
**Control condition** – provision of information about physical activity only
**Motivation condition** – provision of information + motivational BCTs
**Self-regulation condition** – provision of information + motivational BCTs + self-regulatory BCTs
**Habit condition** – provision of information + motivational BCTs + self-regulatory BCTs + habit formation BCTs

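### The mediation path models name no hospital term although the arm-comparison model has one, so a site difference shared by mediator and follow-up activity can modestly inflate false indirect effects

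*Protocol article*

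**What the plan says.** All of the analysis text is in the Study analysis section of the protocol article.

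- **Arm comparison.** A generalized linear mixed model (condition by time) is planned as a "mixed-model design, accounting for nesting within hospital". It serves the primary and secondary outcomes.
- **Mediation.** "Mediation analyses will be conducted using path analytic models", with a bootstrap for multiple mediators. "Each condition will be represented by a dichotomous dummy-coded variable", and "Each condition variable will be set as a predictor of physical activity at follow up". The named constructs (motivation and intention; perceived behavioural control and planning; self-reported habit) enter "as multiple mediators in each analysis, respectively".
- **Covariates in the mediation models.** "Baseline physical activity will be included as a control variable". No other covariate is named, and no hospital stratum or cluster.

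Two design facts matter. Participants "will be recruited from four hospitals in Perth, Western Australia" (Abstract, Methods/Design). The Study design section says that individuals, not hospitals or wards, are randomised.

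**The concern.** The two analyses differ in what randomisation protects. Individuals are randomised, so arm is not systematically tied to hospital, and the arm contrast keeps its error rate even without a hospital term. The arm-to-mediator path has the same protection. The mediator-to-outcome path does not, because nobody is randomised to a level of planning, intention or habit. If some hospitals are higher on both a mediator and follow-up activity, the path coefficient picks up that shared difference unless hospital is in the model.

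At stake is the fifth hypothesis in Study hypotheses, which assigns each condition its own mediators, and the statements about mechanism and active ingredients in the Discussion and Implications. The primary comparison is not at stake.

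**Working it through.** The plan states no figure on this point, so there is none to reproduce. The check has three parts: an approximate formula, a simulation of the indirect effect, and a control run on the arm test.

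**Inputs from the protocol article**
- Four hospitals (Abstract) and individual randomisation (Study design).
- N = 192 recruited and 134 required (Sample size). These agree with the stated 30% dropout: 192 × 0.70 = 134.4.
- A 0/1 condition variable and control for baseline activity (Study analysis). The simulations use a 3:1 split, which is the coding for the motivational component, received by three of the four arms.

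**Assumptions, not in the documents**
- Hospital ICC of 0 to 0.10 in both mediator and activity.
- Correlation of the hospital effects on mediator and activity of 0, 0.5 or 1.
- Arm-to-mediator effect *a* of 0 to 0.8 SD.
- Baseline-to-follow-up correlation of activity of 0.5 within hospital (in the tabulated runs).
- True mediator-to-outcome effect *b* = 0, so any indirect effect *a × b* is false.

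**Step 1: approximate size of the bias.** Take total variances of 1, ICC 0.10 and the same hospital effect on mediator and activity. With four hospitals, the expected within-sample between-hospital variance is 0.10 × 3/4 = 0.075, and each total is 0.90 + 0.075 = 0.975.

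- Baseline carries no hospital effect: *b* ≈ 0.075 / 0.975 = 0.077. With *a* = 0.8, *ab* ≈ 0.8 × 0.077 = 0.062 SD. The simulated mean was 0.059.
- Baseline carries the same hospital effect: the baseline-to-follow-up covariance is 0.075 + 0.5 × 0.90 = 0.525. Then *b* ≈ (0.075 × 0.975 − 0.075 × 0.525) / (0.975² − 0.075²) = 0.03375 / 0.945 = 0.036, and *ab* ≈ 0.8 × 0.036 = 0.029 SD. The simulated mean was 0.025.

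The planned baseline adjustment thus removes roughly half of the bias.

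**Step 2: false-positive rate of the indirect effect.** A 95% Monte Carlo interval for *ab* stands in for the planned bootstrap. There were 1,000 runs per cell, so the Monte Carlo standard error near 5% is √(0.05 × 0.95 / 1000) = 0.7 percentage points. Hospital effects are fully shared (correlation 1). Rates at ICC 0 / 0.02 / 0.05 / 0.10:

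| N | *a* (SD) | No hospital term, baseline carries hospital effect | No hospital term, baseline carries none | Hospital indicators |
|---|---|---|---|---|
| 192 | 0.5 | 4.1 / 4.3 / 5.2 / 7.9% | 3.2 / 4.2 / 8.4 / 21.2% | 3.2 / 3.5 / 3.9 / 4.0% |
| 192 | 0.8 | 5.6 / 5.5 / 7.0 / 10.9% | 3.4 / 6.7 / 13.9 / 27.0% | 5.0 / 4.9 / 4.9 / 6.1% |
| 134 | 0.5 | 3.7 / 3.5 / 3.5 / 5.9% | 3.9 / 4.3 / 6.4 / 13.8% | 3.0 / 2.8 / 3.6 / 2.6% |
| 134 | 0.8 | 5.7 / 6.4 / 5.5 / 8.6% | 5.1 / 5.4 / 10.3 / 19.2% | 4.6 / 3.4 / 5.1 / 5.1% |

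With *a* = 0 the rate is at most 1% in every setting.

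Less extreme settings were also run, with the ICC defined for what remains after baseline adjustment, correlation 0 or 0.5, 3,000 runs per setting and no hospital term:
- *a* = 0.2 or 0.28 SD: 0.4 to 3.3% at every ICC up to 0.10.
- *a* = 0.5 SD, ICC 0.02 or 0.05: 3.0 to 6.5%.
- *a* = 0.5 SD, ICC 0.10: 4.7 to 6.7% with uncorrelated hospital effects, 6.4 to 11.4% with correlation 0.5.

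A further run at N = 192 gave at most 3.5% at *a* = 0.28 SD. For *a* = 0.5 to 0.8 SD it gave 3 to 7% at ICC 0.02 to 0.05 and about 7 to 11% at ICC 0.10, against about 3 to 6% with hospital indicators.

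**Step 3: control run on the arm test without a hospital term.** At N = 192 with 5,000 runs, type I error was 5.3%, 5.4%, 4.8% and 5.1% at ICC 0, 0.05, 0.10 and 0.20. Randomisation protects this comparison, as expected.

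**The case against.** The strongest reply is that the text does not exclude hospital from the path models. A condensed article gives one paragraph to analysis, and the full covariate list of a secondary model is often left to the analysis plan. This stands in part: the omission cannot be read as a decision. But the paragraph does write the path model out, down to predictor, mediators and a named control, directly after naming hospital for the neighbouring model. A suggestion to complete that specification is fair. If a fuller plan already includes hospital, only the wording here needs to change.

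Three further objections stand and limit the point:
- **The indirect effect is what gets tested.** A *t* test of the mediator-to-outcome path alone rejects in about 9 to 12% of null trials at ICC 0.10. A reader might take that as the rate of false mediation claims. It is not: the bootstrap tests *a × b*, which is rarely significant unless the arm also moves the mediator clearly.
- **No ICC is given.** The inflation needs hospital effects that survive baseline adjustment and are correlated between mediator and activity. With independent effects at ICC 0.10 and *a* = 0.5 SD the rate stays at 4.7 to 6.7%.
- **Hospital is only one possible confounder.** Job level, shift pattern and hours worked are recorded (Demographics) and could matter as much.

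**Conclusion.** The point holds as a modest improvement to a secondary analysis. Without hospital in the path models, the indirect effect keeps close to its nominal error rate at a hospital ICC of 0.02, and stays below it when the arm barely moves the mediator. With an arm-to-mediator effect of 0.5 SD or more, the rate reaches about 7% at ICC 0.05 and, at N = 192, about 7 to 11% at ICC 0.10. The ICC, the correlation of hospital effects and the arm-to-mediator effect are all assumptions. The rates of 21 to 27% in the table need a fully shared hospital effect at ICC 0.10 that is wholly absent from baseline activity. They mark an extreme, and the conclusion does not rest on them.

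A reader might go further and infer that the plan leaves hospital out exactly where it matters most, that a single high-scoring hospital is enough to produce apparent mediation, or that staff of one hospital share rosters and so behave alike. The documents support none of these. They give no ICC and do not rank the confounders, and the Participants section admits shift and non-shift staff. Nor does the point touch the primary comparison.

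**What to change.** Add one sentence to Study analysis, after the one on baseline physical activity. It should state that hospital enters as three fixed indicators in both the mediator equation and the outcome equation of every path model, consistent with the mixed model. Fixed indicators suit four hospitals. Resampling within hospital in the bootstrap is optional.

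The cost is three degrees of freedom per equation. For example, the outcome equation of the motivation model has an intercept, condition, two mediators and baseline. Its residual degrees of freedom fall from 192 − 5 = 187 to 184, or from 134 − 5 = 129 to 126. No new data are needed, because the mixed model already requires hospital. The change removes confounding by hospital only. The mediator-to-outcome path stays observational, and the report should say so.

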### Procedure

After screening, eligible participants will be contacted by a study researcher who will arrange a one-on-one meeting (Figure 1, CONSORT flow diagram). During the meeting, the participant will receive a detailed explanation of the study, and its requirements and expectations from the researcher. They will also be provided with an information sheet providing the same information and outlining their rights to confidentiality and to withdraw from the study at any stage without consequence. Once the participant has had the opportunity to confirm their understanding of the project and have any questions answered, they will be asked to sign an informed consent form.

A study researcher will set up and initiate a GENEActiv activity monitor [47] for each participant, including programming the participant’s code number, date of birth, height, and handedness. Each monitor will be programmed to start collecting data from set up. Study participants will be required to wear the monitor on their non-dominant upper arm and will be provided with detailed instructions on how to wear the device. Participants will be instructed to wear it continuously throughout day and night for one week after the first meeting.

Eight days later, participants will meet with the researcher again to return the activity monitor. The study facilitator will check if sufficient data have been collected by the device (i.e., at least five days of wear with a minimum 16 h wear per day) [48]. If the participant fails to wear the activity monitor for the minimum time specified, they will be asked to wear it again for another seven days. At this second meeting, participants will also be asked to complete web-based baseline questionnaires using a provided tablet (Time 1).

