After the second meeting, participants will be emailed a personalised login/password, and link to the website so they are able to login to the web-based *PATHS* study platform used to deliver the tailored intervention messages. Participants will be automatically randomly allocated online in an equal ratio to one of the four possible study conditions; a block randomisation will be used with block size of 16. If allocated to one of the three intervention conditions, they will be able to complete the first intervention session on the website immediately after completing the baseline assessments. If allocated to the control condition, they will receive an email directing them to the *Library* site for physical activity relevant information. The *Library* is a sub-section of the website with non-tailored evidence-based information about physical activity,

Across all conditions, participants will be encouraged to use and interact with the web-based *PATHS* platform for three consecutive months, completing sessions every fortnight. At the end of month three, participants will meet with the researcher and will be provided with a GENEActiv activity monitor to be worn for one week immediately post-intervention to assess physical activity. Participants will meet with the researcher again one week after they received the activity monitor to complete the post-intervention questionnaires and return the activity monitor (Time 2). All researchers collecting the data will be blinded to the allocation of participants’ study condition.

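### The 4 × 2 change model for the primary outcome gives up precision that a common baseline mean, or baseline adjustment, would recover from data already collected

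*Protocol article*

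**What the plan says.** All in the protocol article.

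- **Study analysis, model.** A generalized linear mixed model with four conditions crossed with "2 (time: baseline, 3-month follow-up"), described as a "mixed-model design, accounting for nesting within hospital". Baseline is thus one of the two outcome occasions.
- **Study analysis, contrast.** "Models will be conducting to compare change between conditions of the primary outcome (physical activity"). The same models serve the secondary outcomes.
- **Study analysis, baseline adjustment.** "Baseline physical activity will be included as a control variable". This sentence follows directly on the mediation path models, whose outcome is activity at follow-up. By position it belongs to them.
- **Study analysis, dropout.** "Intention-to-treat (baseline carried forward) will be utilised for missing data from drop-out". A completers analysis is also to be reported.
- **Study design.** "We chose randomisation of individuals within hospitals (rather than randomisation of hospitals or wards").
- **Procedure.** The accelerometer week ends at the second meeting, where the Time 1 questionnaires are also completed: "At this second meeting, participants will also be asked to complete web-based baseline questionnaires using a provided tablet (Time 1"). Allocation is described after that meeting: "Participants will be automatically randomly allocated online in an equal ratio to one of the four possible study conditions". The Measures section places the first accelerometer week before the intervention.

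**The concern.** When baseline is a level of the time factor and each condition has its own mean at each time, the condition-by-time term subtracts each arm's observed baseline mean in full. In an individually randomised trial those baseline means differ only by chance. Subtracting them in full therefore adds noise whenever the correlation between the two measurements is below 1. A model that assumes one baseline mean, or that regresses the follow-up value on baseline, removes only the part of the baseline difference that predicts the outcome.

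What is at stake is precision, not validity. Both estimators target the same effect. The loss would recur in every continuous secondary outcome analysed in the same way. The mediation models already condition on baseline activity, so the plan does for a secondary question what it does not state for the primary one.

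**Working it through.** **Inputs from the protocol (Sample size, Procedure, Study analysis).** d = 0.28; 134 analysed; 30% dropout; 192 recruited, 48 per arm; equal allocation, so 1:3 for control against the pooled intervention arms; alpha 0.05, taken as two-sided. **Assumed:** r, equal variance at both times, dropout unrelated to outcome.

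**The plan's own figures.** 134 / 0.70 = 191.4, rounded up to 192 = 4 × 48. This reproduces. The 134 does not reproduce as a total: the usual two-sided calculation gives 201 per arm (402) at 1:1. At 1:3 it gives 134 in the control arm and 536 in all. That is a separate matter and is not used below. The plan gives no figure for the precision of the 4 × 2 model.

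**Step 1: what the contrast is.** With an identity link and two values per person, a model with free means in every condition-by-time cell gives an interaction equal to the difference in mean change. On simulated data (four arms of 48, random intercept) the three interaction estimates were 0.31946, 0.42239 and 0.50529. The differences in mean change agreed with them to all five decimals.

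**Step 2: variances, in units of σ².**
- Change score: 2(1 − r)
- Baseline-adjusted: 1 − r²
- Ratio, adjusted to change: (1 − r²) / [2(1 − r)] = (1 + r)/2

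For completers at r = 0.5 this is 0.75, and √0.75 = 0.866 (standard error 13% smaller). At r = 0.7 it is 0.85, and √0.85 = 0.922 (8% smaller).

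**Step 3: baseline carried forward.** For 30% of people the follow-up value equals baseline. The effective correlation becomes r′ = 0.7r + 0.3, and the effect is diluted to 0.7 × 0.28 = 0.196.
- r = 0.5: r′ = 0.65, ratio 1.65/2 = 0.825, √0.825 = 0.908 (9% smaller)
- r = 0.7: r′ = 0.79, ratio 1.79/2 = 0.895, √0.895 = 0.946 (5% smaller)

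**Step 4: power, pooled intervention against control.** Power ≈ Φ(δ/SE − 1.96), with SE = √[v(1/n₀ + 1/n₁)] and v from Step 2. Carried forward, r = 0.5: 1/48 + 1/144 = 0.02778.
- Change score: v = 2(0.35) = 0.70, SE = 0.1394, 0.196/0.1394 = 1.406, power 0.29
- Adjusted: v = 1 − 0.65² = 0.5775, SE = 0.1267, 0.196/0.1267 = 1.547, power 0.34

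| r (assumed) | Ratio, completers | Power, 33.5 v 100.5 | Ratio, carried forward | Power, 48 v 144 |
|---|---|---|---|---|
| 0.3 | 0.65 | 0.220 → 0.313 | 0.755 | 0.220 → 0.277 |
| 0.5 | 0.75 | 0.289 → 0.367 | 0.825 | 0.290 → 0.340 |
| 0.7 | 0.85 | 0.441 → 0.502 | 0.895 | 0.442 → 0.483 |
| 0.8 | 0.90 | 0.602 → 0.648 | 0.93 | 0.604 → 0.635 |

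**Step 5: simulation check (4,000 trials per setting).** At r = 0.5 and 0.7 the variance ratios were 0.767 and 0.858 with full data, and 0.823 and 0.902 with carry-forward. The mean estimates of the two methods agreed (0.281 and 0.282 with full data at r = 0.5; 0.196 and 0.195 with carry-forward). The gain therefore brings no bias.

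**The case against.** The strongest reply is that the article does not say the baseline means are free. A model with a common baseline mean is also a condition-by-time mixed model that compares change, and a fuller analysis plan could contain that constraint. This stands as a limit on certainty: a reader might take free baseline means as stated fact, and they are an inference. It does not remove the point. The plan as written, on its standard reading, gives the less precise estimate, and one sentence would settle it.

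Several stronger readings are tempting, and the documents do not support them.

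- **Bias from baseline imbalance.** A reader might infer that chance imbalance distorts the result through regression to the mean. Under randomisation the change-score contrast is unbiased, and its standard error already reflects that imbalance. Lost precision is the only harm.
- **The larger gain throughout.** The 8–13% reduction in standard errors applies to the completers set. In the carried-forward analysis it is 5–9%.
- **Too few hospitals for a random effect.** The text asks only that nesting within hospital be accounted for. It does not say how, and fixed hospital effects would satisfy it.
- **One remedy for every outcome.** The plan names a generalized model. With a non-identity link the change-score identity and the (1+r)/2 ratio hold only approximately, so the figures cannot simply be extended to an outcome such as absenteeism. ANCOVA and the common-baseline model are also not interchangeable in general: ANCOVA does not directly test the within-arm increases in the first hypothesis.

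It can also be said that the power figures are for the pooled comparison, not the four-condition interaction. That is true. The pooled comparison is used because the Sample size section says the trial is powered for it. For complete data, the variance ratio is the same for a contrast between any two arms.

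**Conclusion.** The point holds as a matter of efficiency. As specified, the primary contrast is a valid change-score comparison that is less precise than a baseline-adjusted one at every correlation below 1. For r between 0.5 and 0.7, standard errors would fall by about 5–9% in the carried-forward analysis and 8–13% in completers. Power for the pooled comparison would rise by about 4–5 percentage points under carry-forward and 6–8 in completers.

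This rests on the standard reading of the 4 × 2 model, an identity link, equal variances, dropout unrelated to outcome, and a correlation that the protocol does not give. It also assumes that the baseline accelerometer week, including any repeat week for insufficient wear, is finished before allocation, as the order in Procedure and Measures suggests.

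A reader might infer that better use of baseline rescues the stated power. It does not: for r up to 0.8, power stays below 80% after the change. The 80% claim in the Sample size section needs its own correction.

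**What to change.** In Study analysis, state that for the primary outcome, and for continuous secondary outcomes measured at both times, the longitudinal mixed model will have one baseline mean common to the four arms. That means time and condition-by-time terms with no condition main effect. This form still yields the within-arm changes needed for the first hypothesis.

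As an alternative for the between-arm contrasts only, use ANCOVA of the 3-month value on baseline. For outcomes modelled with a non-identity link, include the baseline value as a covariate.

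The cost is a few sentences. No new data, visits or participants are needed. The change should be recorded before outcome data by arm are seen.

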### Theories of behaviour change and maintenance

Health behaviour change interventions are usually underpinned by psychological theories of behaviour change and maintenance. Many such theories have focused on *motivation* and intentions to explain and change behaviour (e.g., the Theory of Planned Behaviour) [33]. These theories view lack of engagement in health behaviours (e.g., physical activity) as primarily a problem with motivation, such that increasing motivation will directly lead to increases in behavioural participation. The theories also assume that motivation is a function of an individuals’ explicit, consciously-held beliefs about the behaviour [33]. However, theories of *volition* [34] indicate that motivation is a necessary but insufficient condition for behavioural enactment and suggests that volitional strategies (e.g., planning) that operate in a post-decisional manner (i.e. after intentions have been formed) lead to the effective execution of intentions into action because they enable an individual to more effectively recall their intended behaviour via prompts or cues that have been linked to the desired behaviour [35].

Dual process theories offer a broader perspective that integrates *motivational* and *volitional* processes, but also recognises that behaviour may also be influenced by more implicit, non-conscious processes [36–39]. Dual process theories propose that health behaviours are enacted through two processes – the conscious, deliberative processes such as those described in motivational and volitional theories, as well as non-conscious processes that occur automatically, outside an individual’s deliberation. The implicit processes reflect initiating or engaging in actions with very little deliberative, reasoned, and conscious decision making processes outlined in traditional motivational theories. Behaviours that may initially be controlled through deliberative, motivational pathways behaviours can, through a *habit-formation process* become controlled by automatic processes [40]. Habit formation likely occurs through learning of context-behaviour associations via context-dependent repetition of the behaviour usually in the presence of some rewarding contingency [41]. In some cases, the behaviour is enacted because repetition and experience has led the behaviour to occur without the need for any conscious control, as such the behaviour is classed as ‘habitual’ [42, 43].

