### Study hypotheses

We hypothesise significant increases in physical activity between baseline and 3-month follow-up in the three intervention conditions but no change in physical activity levels in the control groupWe hypothesise that increases in physical activity at 3-month follow-up will be greatest in the habit intervention condition with smaller changes for the self-regulation and motivation conditions.We hypothesise that participants allocated to the habit condition will have maintained the physical activity changes over time relative to the self-regulation, motivation, and control conditions at 3-month follow-upWe hypothesise that higher engagement in the program (e.g., frequency of logins, number of sessions completed, reported relevance and usefulness of the sessions content) will lead to greater change in physical activity at 3-month follow-up in all intervention groups.We hypothesise that the effects of the habit condition on physical activity behaviour will be mediated by the self-reported habit development, effects of the self-regulation condition will be mediated by self-efficacy and planning, and the motivation condition will be mediated by the social cognitive variables of attitudes, motivation, and intention.

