In addition, the current study will focus on testing theoretically-distinct groups of techniques and their additive effects on health behavior change. The findings of the study will enable us to evaluate the potential mechanisms by which BCTs derived from motivation, volition and habit theories affect change in health-related behaviour. Our research will also enable us to test the mediators of the intervention effects to increase participants’ physical activity and quality of life, and to reduce work-related stress and absenteeism. We will be able to do this by comparing the effects of each intervention component (e.g., self-regulation) on outcomes mediated by specific theory-based psychological constructs (e.g., planning, self-efficacy) conceptually related to the component.

Personal characteristics of the intervention participants will be assessed to determine for whom the different intervention content is most suitable. Potential moderators of intervention effects will include level of engagement in the program and planning skills. Determining the characteristics of potential users will enable the future matching of participants with the most suitable intervention content. In addition, by providing opportunity for participants to report on the usability of the platform in healthcare professionals, we will be able to ascertain the extent to which the online intervention is feasible in this population and whether it would likely be used by the target population if it were rolled-out on a large scale.

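### In cumulative arms, separate mediation models with one received/not-received dummy mix each component's effect with the others, so they cannot support component-specific mechanism claims

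*Protocol article*

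**What the plan says.** The Study design section builds the arms by addition. The control arm receives information; the motivation arm adds motivational content; the self-regulation arm adds self-regulatory content to that; and the habit arm consists of "provision of information + motivational BCTs + self-regulatory BCTs + habit formation BCTs".

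For mediation, the Study analysis section says "Separate path models will be conducted for each condition" and defines the exposure: "Each condition will be represented by a dichotomous dummy-coded variable (0 = did not receive intervention component, 1 = received intervention component". Each dummy predicts follow-up physical activity through its own mediators, ending with "self-reported habit (habit condition) as multiple mediators in each analysis, respectively". The only adjustment named is this: "Baseline physical activity will be included as a control variable". Neither the other components' dummies nor a comparison of neighbouring arms is mentioned.

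The Discussion says mechanisms will be evaluated by "comparing the effects of each intervention component (e.g., self-regulation) on outcomes mediated by specific theory-based psychological constructs". The Implications section goes on to promise evidence on active ingredients and how they work.

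**The concern.** Habit content is given only to people who also receive motivational and self-regulatory content. A model that contains the habit dummy alone compares the habit arm with the average of the other three arms. That difference includes part of whatever the other two components do. The same holds for the path from the dummy to the mediator, so an indirect effect through self-reported habit can also carry effects of other components.

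The trial expects the other components to work: it hypothesises "significant increases in physical activity between baseline and 3-month follow-up in the three intervention conditions". At stake is the fifth hypothesis, on mediation, and the statement that each component's effect can be traced through its own constructs.

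**Working it through.** **Inputs**
- Component vectors (motivation, self-regulation, habit), from Study design: control (0,0,0), motivation (1,0,0), self-regulation (1,1,0), habit (1,1,1).
- Equal allocation, from Procedure.
- Effect size d = 0.28 for intervention versus control; 134 participants evaluable and 192 recruited, from Sample size. The dropout step reproduces: 134/0.70 = 191.4, rounded up to 192, or 48 per arm. The evaluable number per arm is 134/4 = 33.5, about 34. The plan gives no figure for the mediation analysis, so there is none to reproduce.
- Assumed, because the article gives no values: the effect of each component on self-reported habit, and the habit-activity association.

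**Step 1: what each dummy estimates.** Let m, s and h be the added effects. Relative to control, the arm means are 0, m, m+s and m+s+h.
- Motivation (three arms vs control): (3m + 2s + h)/3 − 0 = m + 2s/3 + h/3.
- Self-regulation (two arms vs two): (2m + 2s + h)/2 − m/2 = m/2 + s + h/2.
- Habit (one arm vs three): (m + s + h) − (2m + s)/3 = m/3 + 2s/3 + h.

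None of these equals its own component's effect unless the weighted sum of the other two is zero. Adjusting for baseline activity does not change this, because under randomisation baseline activity is unrelated to arm.

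**Step 2: size with inert habit content (h = 0).** The protocol's d = 0.28 is the pooled intervention-control contrast, which by Step 1 is m + 2s/3.
- All of the effect from motivation: m = 0.28, s = 0. The habit dummy shows 0.28/3 = 0.09 SD.
- Equal effects: m = s with 5m/3 = 0.28, so m = s = 0.168. The habit dummy shows 0.168/3 + 2(0.168)/3 = 0.168, about 0.17 SD.

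**Step 3: false mediation through habit (h = 0).** Bootstrap mediation was simulated at 34 and 48 per arm. The figures are the percentage of trials with a significant habit indirect effect; where runs with different settings differ, the range is given.

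| Assumed effects | Separate dummy | Joint dummies |
|---|---|---|
| m = s = 0.168; each also raises habit score by 0.168 SD; within-arm correlation 0.3 | 13–18% | about 5–6% |
| m = s = 0.168; no effect on habit score | 4–7% | not needed: already near nominal |
| m = 0.28, s = 0; motivation raises habit score by 0.28 SD; habit-to-activity path 0.4 | 8–9% | 4–5% |
| Larger: m = s = 0.28; habit score raised 0.28–0.30 SD by each | 30–48% | about 5–6% |

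The last row implies a pooled effect of 0.28 + 2(0.28)/3 = 0.47, which is 1.67 times the planned d. It shows the direction of the bias, not its likely size here.

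**Step 4: does joint entry remove it?** With dummies coded (0,1,1,1), (0,0,1,1) and (0,0,0,1) in one model, the three coefficients are m, s and h, that is, motivation minus control, self-regulation minus motivation, and habit minus self-regulation. The habit coefficient then has weights (0, 0, 1).

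**The case against.** Several points on the other side have force.

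- **The main analysis is sound.** A reader might infer that the trial as a whole would declare an inert habit component effective. The article does not support that. Its 4 x 2 mixed model keeps the four conditions separate, so the habit versus self-regulation comparison is available there and would expose an inert component. This limits the point to the mediation models.
- **False mediation is not automatic.** It needs the other components, or the activity they produce, to raise self-reported habit. The article's own theory makes this plausible ("Habit formation likely occurs through learning of context-behaviour associations via context-dependent repetition of the behaviour") but gives no size. Without such an effect the false-positive rate for the indirect effect stays near nominal. The mixing in the total effect does not depend on this.
- **Large effects should not be assumed.** It is tempting to set m = s = 0.28 and quote error rates of 30% or more, but that contradicts the protocol's pooled effect, as shown in the working.
- **The coding should not be misread.** Someone might take each dummy as this arm against all others, which would give the motivation dummy a partly negative weight. The stated definition, received versus did not receive the component, rules that out. Reading it as each arm against control does not rescue the plan either: the habit contrast becomes m + s + h.
- **The fifth hypothesis speaks of conditions, not increments.** A whole-package effect against control would be a fair target for it. But the Discussion claims component effects, and the stated coding delivers neither the package effect nor the increment for the habit and self-regulation arms.

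The Discussion does concede that interactions cannot be tested. That does not cover this problem, which exists even when effects are perfectly additive.

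**Conclusion.** The mediation models are wrong as specified, because the article positively states separate models with one dummy each; this is not a detail left to a fuller analysis plan. The algebra rests only on cumulative arms and equal allocation.

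With inert habit content and the pooled effect held at d = 0.28, the habit model shows a spurious total effect of about 0.09 to 0.17 SD. Its indirect effect is falsely significant in about 5 to 18% of trials, against about 5 to 6% with joint dummies. The upper part of that range rests on an assumed effect of the other components on self-reported habit.

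The component-specific mechanism claims in the Discussion and Implications are not supported by these models. Randomisation, data collection and the primary-outcome model are untouched. It should be fixed, but it does not threaten the trial's primary result.

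**What to change.** Replace the separate single-dummy models by entering all three cumulative dummies in each path model, coded for control, motivation, self-regulation and habit arms as: motivation 0,1,1,1; self-regulation 0,0,1,1; habit 0,0,0,1. Equivalently, specify adjacent-arm contrasts: motivation vs control, self-regulation vs motivation, habit vs self-regulation. Each model can keep its own planned mediators; putting all mediators into one model is not needed to remove the confounding.

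This is a change of wording and needs no new data. The price is precision. Each component's effect then rests on two arms of about 34 to 48. With n per arm and equal variances, the variance of the total-effect contrast rises from (1 + 1/3)/n to 2/n for motivation and habit, so intervals are √1.5 = 1.22 times as wide. For self-regulation it rises from 1/n to 2/n, or √2 = 1.41 times as wide. The Sample size section already says the trial is not powered for differences between the four arms, so these results should be labelled exploratory.
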